### Drug accountability and safety evaluations

Preparation of study drugs will be performed on the basis of authorised drug preparation protocols by the hospital pharmacy. After preparation, the syringes will be labelled according to local guidelines and dispensed to research staff only; no additional labelling will be performed.

The investigator will be responsible for the destruction of the supplies at the study center pursuant to the ICH/GCP (International Conference on Harmonisation of Technical Requirements for Registration of Pharmaceuticals for Human Use/Good Clinical Practice) Guidelines, local regulations, and the investigator’s institutional policies. Clinical supplies will be received by the Academic Medical Center hospital pharmacy at the study site, handled and stored safely and properly, and kept in a secured location with limited access. Clinical supplies are dispensed in accordance with the protocol. The investigator is responsible for keeping accurate records of the clinical supplies, the amount dispensed to and returned by the patients, and the disposition at the end of the study. We will conform with the requirement for adverse experience reporting according to Good Clinical Practice guidelines and local Medical Ethics Committee practice.

### Outcome parameters

#### Primary parameter

The primary parameter is rating of surgical conditions (SRS), as described in Table 2, during the abdominal phase of the operation [2].

#### Secondary parameters

Rating of SRS during thoracic phase of the operation, number of on-demand boluses infused, and indication of on-demand bolus administration.Rating of anaesthesia conditions, including peak and mean respiratory pressures and incidence peak insufflation pressure of more than 35 mm Hg; depth of NBM at the end of surgery, intraoperative cardiac and respiratory incidents; and time until spontaneous breathing and time until extubation after interruption of sedation.Costs: amount of rocuronium used (milligrams), dose of sugammadex needed (milligrams) to reach a TOF of more than 90 %, time to reversal, number of patients (percentage) with recurarization measured 30 min after reversal and consequently the need for additional sugammadex, and duration of surgery and operating room occupancy (expressed in hours and personnel cost per hour) and ICU stay.Perioperative surgical complications.The ability of surgeons and anaesthesiologists to estimate post-operatively to which group the patient was randomly assigned (at the end of each of the two phases).

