### Design

This study is designed as a single-center randomized controlled double-blinded trial. Patients are randomly assigned to receive either continuous infusion of rocuronium 0.6 mg/kg per hour (group 1) or continuous infusion of NaCl 0.9 % 0.06 ml/kg per hour (group 2). This is started immediately after induction. Treatment allocation will be done in a double-blinded fashion (including both the surgeon and the anaesthesiologist), to standard (on indication) versus deep NMB. Blinding will be done by a computerized randomization code. We will randomly assign according to the principle of balanced assignment: the order in which patients are classified to the different groups will be determined in a computer-randomized order. Block randomization will be done and stratified by type of surgery (start in supine or prone position) to correct for any influence of this parameter on the study endpoints. The reasons for withdrawal will be accurately documented in the case report forms. The medication is prepared and labeled by the pharmacy and supplied by the (blinded) researcher to the blinded anaesthesiologist in charge of the patient. Double blinding will be maintained during the study unless the anaesthesiologist in charge needs to unblind the data in case of a medical emergency.

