If indicated by either surgeon or anaesthesiologist, all patients, irrespective of their group assignment, can receive boluses of open-label rocuronium 0.30 mg/kg. The reason for the on-demand bolus is registered. Surgical conditions will be scored immediately before and 5 min after a bolus when requested by the surgeon only, so as not to affect blinding of the surgeons. Indications for bolus infusion are high peak inflation pressure (>35 mm Hg), high abdominal (>15 mm Hg) and thorax (>8 mm Hg) insufflation pressure, and movement, breathing, or straining of the patient. Intra-abdominal pressure will be registered every 30 min from the abdominal CO_2_ insufflation device.

For neuromuscular function monitoring, the TOF-watch SX acceleromyograph (MSD BV, Haarlem, The Netherlands) will be used. During the procedure, a TOF count (situated at the flexor hallucis brevis of the leg) will be done every 30 min at the same time as the evaluation of the surgical conditions and directly before and 5 min after an on-demand bolus [10]. Both the anaesthesiologist and the surgeon will be blinded for the results of this measurement.

When the operation is finished, a TOF count and ratio are done at the ulnar nerve (not blinded). Depth of NMB will be scored as follows: (1) very deep NMB (post-tetanic count, no twitches, (2) deep NMB (post-tetanic count, one or two twitches), (3) moderate NMB (TOF, one or two twitches), and (4) shallow or no NMB (TOF four twitches, ratio of more than 0 %). In patients with a very deep or deep NMB, a TOF is repeated 30 min after infusion of sugammadex to check for recurarization. Based on the TOF count at the end of operation, sugammadex is given at a dose of 16 mg/kg in very deep block, 4 mg/kg in deep NMB, 2 mg/kg in moderate NMB, and 2 mg/kg in shallow NMB. If recurarization is found, an additional dose of sugammadex is given on the basis of the TOF count found at that time. In case of a clinical reason to continue mechanical ventilation after surgery, administration of sugammadex is postponed until one post-tetanic twitch is found. The sugammadex dose needed in case of a very deep block (16 mg/kg) was added to the protocol after 10 patients.

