The reasons for anaesthesiologists not to standardize a deep NMB regime may be the expected need for reversal at the end of the procedure. When employing deep NMB, one has the option to use sugammadex, which is costly, or have the patient on mechanical ventilation post-operatively, which may increase the incidence of pneumonia following surgery [1]. Reversal with (high-dose) neostigmine is usually not favored following these procedures in fear of the cholinergic effects on the newly formed anastomosis, although recent evidence for the adverse effects on anastomotic patency is scarce and the existing data are conflicting [6–8].

Sugammadex has been shown to be a safe and fast alternative to reverse the neuromuscular blocking induced by rocuronium, even when it was administered continuously for up to 5 h [11]. However, as yet, no data on the use of sugammadex after 8–9 h of deep (continuous) neuromuscular relaxation and the incidence of recurarization exist. Therefore, we will register time until TOF of more than 90 % and the incidence of recurarization.

Furthermore, lack of adequate neuromuscular monitoring (e.g., TOF)—in the prone position but especially in the supine position, where both hands are tucked in alongside the body—is challenging to the anaesthesiologist. Hand movements are often inhibited, and TOF counts are unreliable. In view of that, anaesthesiologists and surgeons often disagree about the operating conditions and the ability of the surgeons to judge whether the patient is adequately relaxed or not. We therefore let the surgeons (and anaesthesiologist) “estimate” at the end of the operation to which group the patient was randomly assigned.

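### The timing of the allocation estimate is worded inconsistently, so the anaesthesiologist's last estimate may follow the unblinded end-of-surgery TOF

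*Protocol article*

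**What the plan says.** Three places in the protocol article bear on when the allocation is estimated.

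- Secondary parameters names the outcome as "The ability of surgeons and anaesthesiologists to estimate post-operatively to which group the patient was randomly assigned" and then, in parentheses, times it "at the end of each of the two phases".
- The Discussion says that the surgeons and the anaesthesiologist make the estimate "at the end of the operation to which group the patient was randomly assigned".
- Study procedures and measurements keeps the intraoperative leg TOF from both the surgeon and the anaesthesiologist, but then says: "When the operation is finished, a TOF count and ratio are done at the ulnar nerve (not blinded"). It goes on: "Based on the TOF count at the end of operation, sugammadex is given at a dose of", followed by a dose for each depth of block.

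The Design section promises that "Double blinding will be maintained during the study", with an exception for medical emergencies. The Discussion includes depth of block at the end of surgery among the conditions that anaesthesiologists assess.

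**The concern.** The estimate is meant to show whether blinding held during the operation. The timings given do not agree: the end of the first phase cannot be post-operative, and the Discussion mentions only one point, the end of the operation. Two of the three wordings put the estimate at or after the moment when the unblinded ulnar TOF is taken.

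That reading carries information about allocation. The Abstract and Background say that a continuous infusion may leave a deep block at the end of surgery, and the Limitations section expects some very deep blocks. An anaesthesiologist who has seen the reading and chosen a sugammadex dose from it may guess correctly for that reason alone.

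At stake is how one component of a named secondary outcome is interpreted. An estimate made after the reading could suggest that blinding failed when it had held. The anaesthesiologist does not score the surgical rating scale (SRS), but can call for open-label boluses, so blinding of that role during surgery is worth knowing. If the order of estimate and reading is not recorded, no later analysis can recover it.

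**Working it through.** **1. Order of events, by type of surgery**

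Inputs: the two procedure descriptions under Surgical procedure, and the timing statements set out above.

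| Estimate | Two-stage (abdomen, then thorax) | Three-stage (thorax, abdomen, then neck) |
|---|---|---|
| End of first phase | Before the ulnar TOF | Before the ulnar TOF |
| End of second phase | Coincides with the end of the operation, because the thoracic phase finishes with wound closure; order against the TOF not stated | Before the ulnar TOF if taken when the abdominal phase ends, because cervical work follows |
| Single estimate at the end of the operation (Discussion wording) | Order not stated | Order not stated |

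Under the phase-end wording, the exposed estimate is the second one in two-stage patients. Under the Discussion wording, it is the only estimate in every patient, and no first-phase estimate would exist to compare it with.

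**2. Who sees the reading**

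The anaesthesiologist assesses depth of block at the end of surgery, and the reversal dose depends on the TOF. No section says that surgeons are given the reading or the dose, and none says that they are kept from it.

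**3. Possible size (illustration only)**

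The documents give no rate of deep block at the end of surgery and no figure on this outcome to reproduce. Assumptions: 33 patients per arm (66 in total); blinding during surgery perfect; and an estimate of infusion whenever the block is deep or very deep, otherwise of on-demand.

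Expected correct = 33 × p1 + 33 × (1 − p2), where p1 and p2 are the shares ending in deep or very deep block in the infusion and on-demand arms. The last column is the exact two-sided binomial P against 50%.

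| p1 | p2 | Expected correct | Rounded, of 66 | Share | P |
|---|---|---|---|---|---|
| 90% | 20% | 29.7 + 26.4 = 56.1 | 56 | 85% | 6.9e-9 |
| 80% | 20% | 26.4 + 26.4 = 52.8 | 53 | 80% | 7.2e-7 |
| 60% | 30% | 19.8 + 23.1 = 42.9 | 43 | 65% | 0.019 |
| 50% | 50% | 16.5 + 16.5 = 33.0 | 33 | 50% | 1.0 |

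The share correct depends only on the gap p1 − p2, and the effect vanishes when the arms end at the same depth.

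**The case against.** A reader might infer that this outcome measures end-of-surgery block instead of blinding, and so cannot be interpreted at all. The documents do not support that, for these reasons.

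- The sentence that names the outcome also gives phase-end timing. An estimate at the end of the first phase always precedes the ulnar TOF. In three-stage patients the second can do so too.
- The order of the last estimate and the TOF is not stated. It is not shown to be wrong. The timeline figure and the registration forms are not available and may settle it, and an article often leaves that level of detail to the full protocol.
- Surgeons alone score the SRS, and the Limitations section gives judging bias in the SRS as the purpose of the surgeons' estimates. That surgeons learn the reading is conjecture.
- The article says only that continuous infusion might leave a deep block and that some patients may have a very deep one. Boluses of rocuronium are open to both arms, which weakens the link with allocation.
- The rates in the illustration are assumed, and the article sets no threshold at which blinding would be declared broken.

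All of these stand, and they confine the point to the anaesthesiologist's last estimate. They do not remove it. The conflict between the timings is in the text itself, and the Discussion wording, taken alone, provides no early estimate. Missing form-level detail would be no finding by itself, but contradictory timing around an unblinded reading is one.

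**Conclusion.** The point holds in a limited form. Secondary parameters and the Discussion give timings that cannot all be true, and together with the unblinded ulnar TOF they allow the anaesthesiologist's last estimate to be informed by block depth and by the sugammadex dose chosen from it. This concerns chiefly two-stage patients, or all patients if the Discussion's single time point is the one used.

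The size is unknown. Under the assumed rates, 65% to 85% of estimates would be correct with blinding during surgery intact, and 50% if the arms ended at the same depth. These figures rest on estimates that simply follow the TOF and on block rates that the documents do not supply, so they show direction only.

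The primary SRS comparison is not directly affected, because the anaesthesiologist does not score it. First-phase estimates, where collected, remain valid evidence on blinding during surgery, and surgeons' estimates do too unless they learn the reading.

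**What to change.** Reconcile Secondary parameters with the Discussion, and drop the description of the estimate as post-operative. State that surgeons and anaesthesiologist each record an estimate at the end of each of the two phases, and that the last is written down before the ulnar TOF is read and before sugammadex is given. Add the same order to Study procedures and measurements.

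Use only these estimates for the blinding outcome. Report any estimate made after the reading separately, as not informative about blinding during surgery. For patients already treated, report whether the order can be established from the forms.

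The cost is one line on the registration form and a sentence in the protocol. No measurement, dose or other part of clinical management changes.

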#### Exploratory parameters

Outcome parameters are ICU/post-anaesthesia care unit (ICU/PACU) and hospital length of stay, need for re-intubation, post-operative surgical complications (bleeding, anastomotic leakage or bowel perforation, wound infections or sepsis, or re-operations), and pulmonary complications (pneumonia, pneumothorax, pleural effusion, or atelectasis). Pain numerical rating scores will be collected until dismissal ICU/PACU with a maximum of 24 h post-operatively.

These parameters are collected by means of registration forms during the procedure and on the following day. All other data will automatically be recorded by our Patient Database Management System. Hemodynamic monitoring will consist of stroke volume; stroke volume variation; heart rate; diastolic, systolic, and mean arterial pressure; systemic vascular resistance; central venous pressure; cardiac output; and cardiac index (EV1000; Edwards, Irvine, CA, USA). In addition, peripheral capillary oxygen saturation (SpO_2_), end-tidal carbon dioxide (etCO_2_), insufflation pressure, and mean airway pressure will automatically be recorded. Post-operative surgical complications will be prospectively collected.

### Patient flow chart

Figure 1 shows the different phases in data collection during this study in a timeline.

**Fig. 1 Fig1:**
[figure not shown]
Study timeline. The different steps of the study and registrations over time, starting with admittance of the patient to the hospital until dismissal to home, are shown. Informed consent forms and study information are supplied to the patient before admittance. The signed forms are retrieved at the day of admittance. *ICU/PACU* intensive care unit/post-anaesthesia care unit, *NM* neuromuscular, *OR* operating room

### Other anaesthesia procedures

During the study, patients receive standard of care pre-operatively and post-operatively. The surgical procedure will not be changed. Also, induction of anaesthesia, the use of opioids, blood pressure treatment, fluid infusion, and mechanical ventilation will be standard of care.

#### Preparations

Patients will remain fasted for solid foods for 6 h and clear fluids for 2 h. Two hours prior to surgery, two sachets of preOp drink (Nutricia, Dublin, Ireland) or lemonade are given. Blood is drawn for blood type and cross-match analysis. A cannula is inserted into a vein on the right or preferably left hand or lower arm.

Prior to the operation, the patient is transported to the operating room, where a thoracic epidural is inserted with an antiseptic technique in a sitting position. The skin is anaesthetized with lidocaine 2 %, and the Tuohy needle is positioned with loss of resistance or hanging drop technique at a level of Th 6–7 or both.

#### Induction of anaesthesia

In the operating room, general anaesthesia is induced with propofol (approximately) 2–3 mg/kg, sufentanil for analgesia and 1.0 mg/kg rocuronium for paralysis. The trachea is intubated and the lungs are mechanically ventilated with pressure-regulated volume control.

After induction, general anaesthesia is maintained with sevoflurane at a minimal alveolar concentration of 1 and, when needed (on the basis of signs of pain), additional boluses of sufentanil. An arterial line (into the right or left brachial artery), a right subclavian tri-lumen central line, and a double-lumen gastric tube are placed. A urinary catheter is inserted (suprapubic in men). The epidural catheter is loaded with 10 ml bupivacaine 0.25 % in two tempi. One hour later, a continuous infusion of bupivacaine 0.25 % is started (0.08–0.1 ml/kg per hour). In case of a failed epidural, intravenous (i.v.) ketamine (bolus 0.25 mg/kg, maintenance 0.1 mg/kg) continuously is started in combination with i.v. sufentanil continuously 0.5–1 mcg/kg per hour. Cefazoline (Kefzol®) 2 g and metronidazol (Flagyl®) 500 mg are given prior to incision. Cefazoline is repeated according to the national antibiotic guidelines.

#### Surgical procedure

##### Two-stage thoracolaparoscopic esophagectomy (Ivor Lewis procedure)

The patient is placed in a supine position. A laparoscopy is performed by using 5 trocars and a maximum pressure of 15 mm Hg. During laparoscopy, a lymphadenectomy is performed (hepatoduodenal ligament, common hepatic artery, celiac trunk, splenic artery, splenic hilum, paracardial left and right), the greater curvature is mobilized, identifying and sparing the right gastro-epiploic vessels, and a gastric tube (3 cm wide) is created by using a linear stapling device. A jejunostomy catheter is placed approximately 20 cm distal of Treitz ligament, the abdominal phase is terminated, and the incisions are closed (fascia and skin).

Next, the patient is repositioned to a prone position. A thoracoscopy is performed by using 4 trocars and a maximum insufflation pressure of 6–8 mm Hg. The thoracic esophagus is mobilized, and a lymphadenectomy is performed (stations 4, 5, 7, 8, 9, and 10 according to the American Joint Committee on Cancer classification for esophageal cancer). The arch of the azygos vein is divided by using a vascular stapling device. The thoracic duct is transected at the level of the diaphragm and arch of the azygos vein by using 10-mm endoclips and excised with the specimen. The esophagus is divided just cranial to the level of the arch of the azygos vein. The specimen and gastric tube are retrieved in the thorax. A minithoracotomy (5 cm) is performed through which the specimen is resected. An anastomosis is created by using a circular stapling device. The anastomosis may be subsequently sutured with interrupted Vicryl 3.0 sutures. The anastomosis is concealed under the pleura, and an omental wrap is placed around the anastomosis. A nasogastric tube is placed in the gastric tube. After placement of a thoracic drain, the thoracoscopy wounds are closed (muscles and skin).

##### Three-stage thoracolaparoscopic esophagectomy (McKeown procedure)

If a subtotal esophagectomy with high paratracheal lymph node dissection (including station 2) is indicated, a three-stage procedure will be performed. A thoracoscopy is performed first, followed by a laparoscopy. Eventually, a left cervical incision is performed on the ventral border of the sternocleidomastoid muscle, and the cervical esophagus is mobilized and transected with attention for the recurrent laryngeal nerve on both sides. The specimen is retrieved intra-abdominally and removed. The gastric tube is created and pulled up through the mediastinum, and a cervical end-to-end anastomosis is created by using PDS 3.0 intermittent sutures. A nasogastric tube is positioned in the gastric tube. The cervical incision is closed with an intracutaneous suture.

#### Post-operative care

Depending on American Society of Anesthesiologists (ASA) classification, patients will go either to the PACU (ASA 1 or 2) or to the ICU (ASA 3 or higher). The endotracheal tube will be removed as soon as possible after stopping sedation, either in the operating theatre or after arrival in PACU/ICU. Numerical pain rating—on a scale from 0 (no pain) to 10 (most severe pain imaginable)—will be collected each hour.

### Sample size calculation

The sample size is based on an article by Martini et al. [2], who showed a difference of 0.7 points on the SRS and a standard deviation (SD) of 0.4. However, compared with the retroperitoneal surgery studied in that article, the current procedure of esophagectomy is anticipated to have more sources of variability for the surgical conditions. This may reduce the benefit or effect size of treatment to some degree but in particular will increase the variability, even when adjusting for body mass index and the presence of previous procedures, as other factors cannot be effectively controlled. Table 3 shows a range of plausible effect sizes and (adjusted) SDs of the SRS. A sample size of 60 in total would provide a power of 90 % to show a mean difference of 0.6 with a standard deviation of 0.7 and a two sided alpha level of 0.05. This mean difference is slightly lower than observed in the study by Martini et al of 0.6 points on the SRS and a somewhat increased SD of 0.7 points on the SRS. A drop-out of 10 % is expected and therefore we will include 66 patients. After withdrawal of informed consent before the operation but after randomization, the subject will be replaced by a new patient.

**Table 3 Tab3:** Range of plausible effect sizes and (adjusted) standard deviations of the SRS

Mean group difference	Standard deviation			
	0.5	0.6	0.7	0.8
0.5	23	32	43	55
0.6	16	23	30	39
0.7	12	17	23	29

Sample size per group by a range of mean group differences and standard deviations (SDs) on the surgical rating scale (SRS) at 90 % power. A sample size of 60 in total would provide a power of 90 % in case the effect size is slightly lower as observed in Martini et al. [2] of 0.6 points on the SRS and a somewhat increased SD of 0.7 points on the SRS. A drop-out of 10 % is expected and therefore we will include 66 patients

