### Statistical analysis

The data analysis will be based on an intention-to-treat approach. Baseline continuous variables will be summarized by using mean with SD or median with interquartile range as appropriate. Categorical variables will be summarized by using percentage and number of patients. The SRS will be measured repeatedly. These repeated measurements will be summarized to a mean for every patient. These values will follow a normal distribution and therefore be tested by using a Student’s *t* test. A two-sided *P* value of less than 0.05 will be considered statistically significant. The difference in SRS between the two groups will further be examined by using a general linear model. Covariates will be analyzed univariately. Covariates will be included in a multivariable analysis if the univariate *P* value is less than 0.20. A backward selection process will be used to achieve the most optimal model.

Covariates to be considered are anaesthesia- or surgery-related (for example, timing of abdominal and thoracic phase, drug dosages, use of epidural anaesthesia, and duration of surgery) and patient-related (for example, surgical history, age, weight, and body mass index). Patients with less than three surgical rating scores because of early termination of the surgical procedure will be excluded in a secondary analysis. Additional analyses will be performed on the secondary outcome parameters. No interim analysis will be done; the study will be terminated after enclosure of the last patient. Because of the amendment in sugammadex dose, the first 10 patients will be excluded for the cost analysis only. A sensitivity analysis, including the first 10 patients, will be performed.

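### The planning SDs are labelled adjusted but the main SRS test is an unadjusted t test; if 0.7 is a residual SD, the stated 90% power is too high for that test

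*Protocol article*

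**What the plan says.** Under Sample size calculation, the protocol article starts from a cited study "who showed a difference of 0.7 points on the SRS and a standard deviation (SD) of 0.4". It expects more variability in oesophagectomy, "even when adjusting for body mass index and the presence of previous procedures, as other factors cannot be effectively controlled". The next sentence reads "Table 3 shows a range of plausible effect sizes and (adjusted) SDs of the SRS", and the title of Table 3 repeats the bracketed word. The size chosen is then justified: "A sample size of 60 in total would provide a power of 90 % to show a mean difference of 0.6". The SD entered there is 0.7, and the test level is 5%, two-sided. The same paragraph also calls the 0.7 "a somewhat increased SD of 0.7 points on the SRS".

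Under Statistical analysis, each patient's repeated SRS scores are averaged. The article continues "These values will follow a normal distribution and therefore be tested by using a", and the test it names at that point is Student's t test, with no covariates. A general linear model comes after it as a further look at the group difference. Covariates enter that model if their univariate P value is below 0.20 and are then subject to backward selection. Body mass index and surgical history are named only as examples of candidates.

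Under Design, randomisation is in blocks and stratified by type of surgery (start supine or prone).

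**The concern.** The error term of a two-sample t test is the full within-group SD of the outcome. The error term of a covariate-adjusted model is the SD left once the covariates have explained their share, and it is smaller whenever they explain anything. A sample size computed with the second SD overstates the power of the first test.

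The text invites that worry. It speaks of adjusting for two named covariates and in the next sentence calls the tabulated SDs adjusted. The 0.7 behind the 90% claim is one of the columns of that table. Yet the main test adjusts for nothing, and even the follow-up model does not guarantee that either covariate is included. At stake is whether the trial has the power it states for its main comparison, and whether any planned analysis is sure to use the variance on which it may have been sized.

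**Working it through.** **Inputs from the protocol article (Sample size calculation).** Difference 0.6, SD 0.7, two-sided alpha 0.05, power 90%, 60 evaluable patients. With balanced assignment (Design) that is n = 30 per group.

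**Input not in the article.** R², the share of within-group variance of the per-patient mean SRS explained by body mass index and previous procedures. It is assumed below, over a range.

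**Step 1: reproduce the stated figure.** For a two-sample t test, df = 2n − 2 = 58 and the noncentrality is δ = 0.6 / (0.7 × √(2/30)) = 3.32. The two-sided 5% critical value is 2.00. Noncentral t power is 90.4%, and 30 is the smallest n per group that reaches 90%. All 12 cells of Table 3 reproduce exactly in the same way. The arithmetic is therefore sound for a plain t test whose error SD is the tabulated value. What it cannot show is whether that value was meant as a raw or a residual SD.

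**Step 2: if 0.7 is the raw SD.** The t test has 90.4% power, as stated.

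**Step 3: if 0.7 is the residual SD.** The t test works with SD_raw = 0.7 / √(1 − R²). For example, at R² = 0.20, SD_raw = 0.7 / √0.80 = 0.78, δ = 0.6 / (0.783 × √(2/30)) = 2.97, and power is 83.1%.

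| Assumed R² | SD faced by the t test | Power, 30 per group | n per group for 90% |
|---|---|---|---|
| 0 | 0.70 | 90.4% | 30 |
| 0.05 | 0.72 | 88.9% | 32 |
| 0.10 | 0.74 | 87.2% | 33 |
| 0.20 | 0.78 | 83.1% | 37 |
| 0.30 | 0.84 | 78.0% | 42 |

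Table 3's own next column, SD 0.8, corresponds to R² = 1 − (0.7/0.8)² = 0.23. There the power with 30 per group is 81.5%, and the table itself asks for 39 per group.

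**Step 4: allowance from the 66 enrolled.** If nobody dropped out (33 per group), power would be 90.2% at R² = 0.10 and 86.6% at R² = 0.20. This is a best case, because the article expects 10% drop-out.

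**The case against.** A reader might infer that the 0.7 has been shown to be a covariate-adjusted SD, so that the 90% is simply wrong for the t test. The article does not support that. The word adjusted stands in brackets and is not defined, and the column header of Table 3 says only standard deviation. Wherever 0.7 itself is given, it is called a standard deviation or a somewhat increased one, measured against the cited study's 0.4, which the article does not describe as adjusted. The bracketed word could mean that 0.4 was revised upward for a more variable operation, which is what the paragraph does. Table 3 also matches a plain t test cell for cell, so the test calculated and the test planned are the same.

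The size of any loss is assumed throughout, and at R² of 5% it is about 1.5 points. The planning SD is itself a judgement: it was raised from 0.4 to 0.7, the difference was lowered from 0.7 to 0.6, and SDs up to 0.8 are displayed. An unadjusted t test followed by an adjusted model is also a valid design.

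All of this stands, and it makes the point conditional. It does not remove it. The sentence just before the label uses adjusting in the covariate sense and names the covariates, so residual SD is the natural reading, and nothing in the article shows that 0.7 is raw.

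**Conclusion.** The point holds conditionally. As written, the label on the planning SDs and the unadjusted main test do not fit together, and the article does not resolve which SD 0.7 is.

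- If 0.7 is raw, or if the two covariates explain nothing, the stated 90% is right.
- If 0.7 is residual, the direction is certain: power for the t test is overstated. The loss is roughly 1.5 points at an R² of 5%, 3 points at 10%, 7 points at 20% and 12 points at 30%, measured from 90.4% with 30 per group. It rests wholly on the assumed R².

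The stronger statement, that the sample size belongs to an adjusted analysis and the t test cannot deliver 90%, goes beyond the text. This is not a detail left to an analysis plan, because the article fixes both the planning SD and the test. It should be put right, but it does not threaten the validity of the comparison.

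**What to change.** Preferred: make the primary analysis a linear model of per-patient mean abdominal-phase SRS on treatment, type of surgery, body mass index and previous surgery. All terms are fixed in advance, with no univariate screen and no backward selection, and the t test is kept as supportive. Type of surgery plays no part in the SD argument; it belongs in the model because randomisation is stratified on it. This matches the analysis to an adjusted SD if that is what 0.7 is. If 0.7 is raw, the model gains precision to the extent that the covariates are prognostic.

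Alternative: if the t test stays primary, add a sentence saying whether 0.7 is the raw or the residual SD of the per-patient mean. If it is residual, restate the power on the unadjusted SD as a range over stated values of R².

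Cost: wording in the protocol and analysis plan. The stratification factor and both covariates are already named in the article. Neither option adds patients.
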